# Prospective randomised trial examining the impact of an educational intervention versus usual care on anticoagulation therapy control based on an SAMe-TT_2_R_2_ score-guided strategy in anticoagulant-naïve Thai patients with atrial fibrillation (TREATS-AF): a study protocol

**DOI:** 10.1136/bmjopen-2021-051987

**Published:** 2021-10-07

**Keywords:** cardiology, qualitative research, health economics

## Abstract

**Introduction:**

The burden of atrial fibrillation (AF) in Thailand is high and associated with increased morbidity, mortality and healthcare costs. Vitamin K antagonists (eg, warfarin), commonly used for stroke prevention in patients with AF in Thailand, are effective but are often suboptimally controlled. We aim to evaluate the impact of an SAMe-TT_2_R_2_ score-guided strategy and educational intervention compared to usual care on anticoagulation control expressed by the time in therapeutic range (TTR) at 12 months, in anticoagulant-naïve Thai patients with AF.

**Methods and analysis:**

Multicentre, open-label, parallel-group, randomised controlled trial conducted in Thailand among adult patients (age: 18 years) with AF who are anticoagulant naïve. Patients will be randomised to one of two groups; an SAMe-TT_2_R_2_ score-guided strategy with educational intervention and usual care versus usual care alone. The planned follow-up period is 12 months. The primary outcome is TTR at 12 months. Secondary outcomes include: (1) TTR at 6 months; (2) thromboembolic and bleeding events at 12 months; (3) composite major adverse cardiovascular events at 12 months; (4) change in patients’ knowledge of AF between baseline and 6 months and 12 months; (5) cost effectiveness; (6) quality of life at baseline, 6 months and 12 months using EQ-5D-5L (Thai version) and (7) patient satisfaction/perceptions of the TREAT intervention. An embedded qualitative study will assess patient perceptions of the TREAT intervention.

**Ethics and dissemination:**

The study has been approved by the Ethical Review Committee, Ministry of Public Health of Thailand, and registered in the Thai Clinical Trials Registry. The results of this trial will be submitted for publication in a peer-reviewed journal. Participants will be informed via a link to a preview of the publication. A lay summary will also be provided to all participants prior to publication.

**Trial registration number:**

TCTR20180711003.

Strengths and limitations of this studyWarfarin remains the default therapy for stroke prevention in atrial fibrillation (AF) in many countries, but is often suboptimally managed.A one-time structured educational-behavioural intervention (TREAT intervention) among those predicted to be less likely to achieve optimal control may be a simple and cost-effective adjunct management strategy, which could help improve time in therapeutic range.This prospective individually randomised controlled trial in anticoagulant-naïve patients with AF aims to assess whether the application of an SAMe-TT_2_R_2_ score-guided strategy and TREAT intervention plus usual care could improve anticoagulation control with warfarin.The study design has a multidisciplinary team approach, and the efficacy, safety, patients’ satisfaction as well as cost effectiveness will be assessed.One challenge of the study, if implemented, is to standardise the quality of usual care and TREAT intervention among centres.

## Introduction

Atrial fibrillation (AF) is associated with decreased quality of life, and increased mortality and morbidity from stroke/thromboembolism.^1 2^ Incidence of AF has been increasing in developing countries, including Thailand, partly due to the rapid change of population dynamics towards an ageing society.^3 4^ The hospitalisation rate for Thai patients with AF was high (15.5 per 100 000 person-years), with a high mortality (44.0% after 72-month follow-up (average 46 months)).^5^ The high burden of AF in Thailand is also associated with similarly high healthcare costs.^6^

Appropriate oral anticoagulation, either with a vitamin K antagonist (VKA, eg, warfarin) or with a non-VKA oral anticoagulants (NOAC), is essential for effective stroke prevention in patients with AF with one or more stroke risk factors.^7^ Despite the advantages of NOAC over VKA, the access of NOAC are generally limited due to cost. Hence, VKAs are widely used globally.^8 9^ In Thailand, warfarin is the default therapy for stroke prevention in AF but is often suboptimally managed due to the many inherent limitations associated with this drug, including diet, drug and alcohol interactions and difficulties with anticoagulation monitoring. Recent data from retrospective cohort studies, along with a nationwide registry, suggested that the average time in therapeutic range (TTR) among patients with AF in Thailand ranged from 50% to 55%.^10–13^ Those with suboptimal anticoagulation control, TTR <65%, had a twofold–threefold increased risk of stroke, major bleeding and death compared with those with TTR ≥65%.^12^ As a result, strategies to improve TTR control are clearly needed and would likely have a major impact on preventing these adverse events.

TTR is influenced by numerous modifiable and non-modifiable factors, but the more common clinical factors have been used to formulate the SAMe-TT_2_R_2_ score (table 1).^14^

**Table 1 T1:** Components of the SAMe-TT_2_R_2_ score

Components		Points
**S**	Sex (female)	1
**A**	Age (<60 years)	1
**Me**	Medical history*	1
**T**	Treatment (interacting drug, eg, amiodarone)	1
**T**	Tobacco use (within 2 years)	2
**R**	Race (non-Caucasian)	2
Maximum total		8

SAMe-TT_2_R_2_ scores 0–2: the patients with AF likely to achieve and maintain optimal TTR, and SAMe-TT_2_R_2_ scores >2: the patients with AF likely poorer responders.

*More than two of the following: hypertension, diabetes mellitus, coronary artery disease/myocardial infarction, peripheral atrial disease, congestive heart failure, previous stroke, pulmonary disease and hepatic or renal disease.

AF, atrial fibrillation; TTR, time in therapeutic range.

Several observational studies including those conducted in Asian populations, have demonstrated that an SAMe-TT_2_R_2_ value of >2 is predictive of poor TTR, all-cause mortality and the composite endpoint of thromboembolic events, major bleeding and mortality.^13 15–17^ By identifying those who are at risk of poor TTR, targeted efforts to improve TTR can be effectively provided to the vulnerable group. If TTR can be improved to >65%, VKAs can provide comparable efficacy and safety to that seen with NOACs.^18 19^ Previo studies have demonstrated that many patients with AF possess little knowledge about AF and do not understand the risks/benefits of OAC,^20–25^ and this may contribute to poor international normalised ratio (INR) control.

We have previously shown that an educational-behavioural intervention (TREAT, ISRCTN93952605) significantly improved TTR 6 months after warfarin initiation compared with usual care alone (78.5% vs 66.7%, respectively; p=0.01).^26–28^ Thus, a one-time structured educational-behavioural intervention among those predicted to be less likely to achieve good INR control may be a simple and cost-effective adjunct management strategy, which could help improve individual TTR. Increased patient understanding of disease and treatment, and a reduction of adverse events, may improve quality of life.

We, therefore, conducted a prospective individually randomised controlled trial (RCT) in anticoagulant-naïve Thai patients with AF to assess whether the application of an SAMe-TT_2_R_2_ score-guided strategy and TREAT intervention^26–28^ plus usual care could improve anticoagulation control with warfarin (measured by percentage TTR) at 12 months (primary outcome) compared with usual care alone.

### Objectives

The primary objective of this study is to evaluate the impact of an SAMe-TT_2_R_2_ score-guided strategy and educational intervention (plus usual care) compared with usual care alone, on patient’s anticoagulation control with warfarin, as measured by the TTR at 12 months, in anticoagulant-naïve Thai patients with AF. As secondary objectives, we aim to evaluate the impact of this intervention on patient knowledge, TTR at 6 months, thromboembolic and bleeding events and the composite major adverse cardiovascular events (MACE). We will also perform analysis to evaluate the cost effectiveness of the intervention and investigate patients’ satisfaction and acceptance of the TREAT intervention using a brief questionnaire and further in a qualitative sub-study.

## Methods

### Study design and setting

This is a multicentre, open-label, paralleled-group, RCT conducted among adult Thai patients (age: ≥18 years) with AF who are anticoagulant naïve. Patients who are eligible for stroke prevention according to the ESC Guidelines for the diagnosis and management of AF^1^ (men with CHA_2_DS_2_VASc score ≥1; women with CHA_2_DS_2_VASc score ≥2) will be randomised to one of two groups, either an SAMe-TT_2_R_2_ score-guided strategy (see table 1) and educational intervention plus usual care versus usual care alone. The planned follow-up period is 12 months. Study sites are seven public hospitals across six provinces (Bangkok, Chiang Mai, Chiang Rai, Lampang, Khon Kaen and Nakhon Ratchasima) in Thailand. To promote generalisability of our findings, these seven hospitals are a combination of three university hospitals (Maharaj Nakorn Chiang Mai Hospital, Siriraj Hospital, and Queen Sirikit Heart Centre of the Northeast) and four secondary/tertiary care hospitals (Maharat Nakhon Ratchasima Hospital, Chiang Rai Prachanukroh Hospital, Nakornping Hospital and Lampang Hospital). The study sites and investigators are listed in online supplemental appendix 1. The study protocol was approved by the Institutional Ethical Committee of each study site and by the Institutional Review Board (IRB) of the Ministry of Public Health, the Royal Government of Thailand (Central Research Committee (CREC) number: COA-CREC 007/2020) and registered with the Thai Clinical Trials Registry.

10.1136/bmjopen-2021-051987.supp1Supplementary data

### Participants

Newly diagnosed adult patients with AF identified and referred from cardiology, internal medicine, family medicine and general clinics at the hospitals and referrals from primary care will be eligible for enrolment into the study.

### Eligibility criteria

Patients must meet all of the following inclusion criteria to be eligible for randomisation:

≥18 years of ageNewly diagnosed patients with non-valvular AF.ECG-documented AFWarfarin eligible (men with CHA_2_DS_2_VASc score ≥1; women with CHA_2_DS_2_VASc score ≥2)Warfarin naïve (no treatment with anticoagulation within the past 12 months; treatment may have started within the prior 28 days from randomisation).Able to comply with scheduled visits, treatment plan and laboratory testsAble to give informed consent and comply with study protocol (with support of a carer)

Patients will be excluded from participation if they present with any of the following:

Any contraindication to oral anticoagulationProsthetic cardiac valve or significant valvular heart disease with an indication for heart surgeryLikelihood of intermittent or permanent discontinuation of warfarin during follow-up (eg, major surgery or post-AF ablation)Known active malignancy with a life expectancy less than 5 years.Diagnosed significant cognitive impairment preventing provision of informed consent and/or able to comply with the study protocol.Any disease likely to cause death within 12 months.

The study was originally designed to enrol the patients within 5 days of warfarin treatment; however, the average referral time was 14 days. The trial steering committee agreed to extend the duration between starting warfarin and randomisation to 28 days to improve recruitment rate, external validity and generalisability of the trials. The amended study protocol was approved by the Institutional Ethical Committee of each study site and by the IRB of the Ministry of Public Health, the Royal Government of Thailand and updated in the Thai Clinical Trials Registry.

### Randomisation

After participant eligibility has been confirmed and informed consent has been provided, the participant will be randomised into the trial. Randomisation will be done using a web-based platform with blinded allocation. Randomisation will be stratified based on centre, sex (male or female) and baseline SAMe-TT_2_R_2_ score (0–2, 3–5 and 6–8). Participants will be randomised at the level of the individual in a 1:1 ratio to either the SAMe-TT_2_R_2_ score-guided strategy and educational intervention plus usual care (intervention group) or usual care alone (figures 1 and 2). Group 1 is the usual care group using warfarin (control group). For Group 2, the patients are further divided into two groups. Group 2a are patients with an SAMe-TT_2_R_2_ score of 0–2 who will receive warfarin plus usual care. Group 2b are patients with an SAMe-TT_2_R_2_ score of >2 who will receive warfarin plus the TREAT education-behavioural intervention as an adjunct to their regular INR monitoring, to improve their TTR.

**Figure 1 F1:**
[figure not shown]
Study design and recruitment. Group 1: usual care using warfarin (control). Group 2: care pathway designated based on stratification of patients using the SAMe-TT_2_R_2_ score (warfarin plus usual care). Group 2 care pathways: Group 2a: SAMe-TT_2_R_2_ score 0–2 (warfarin plus usual care). NB: usual care would include management in the anticoagulation clinic, and patient information about AF and need for warfarin by a healthcare professional using the standard warfarin education checklist. Group 2b: SAMe-TT_2_R_2_ score >2 (warfarin plus intensive TREAT education-behavioural intervention as an adjunct to their regular INR monitoring to improve their TTR on warfarin). AF, atrial fibrillation; OAC, oral anticoagulants; TTR, time in therapeutic range.

**Figure 2 F2:**
[figure not shown]
Timing of randomisation, study visits and follow-up.

### Trial intervention

As described previously, the TREAT intervention is a patient-centred intervention for patients with AF co-developed through the integration of theoretical and clinical frameworks, and patient feedback.^26 27^ This behaviour-change intervention package consists of an educational booklet, diary, worksheet and a DVD for reinforcement. The educational booklet covers AF causes and consequences, warfarin and its metabolism, stroke risk and risk of bleeding on treatment and lifestyle changes (diet, alcohol and lifestyle change). The patient DVD contains health professionals and ‘expert patient’ narratives that covers AF causes, consequences, side effects, treatment options, warfarin, INR monitoring, lifestyle changes, along with common psychological and physical barriers to anticoagulation that patients may experience. The patient worksheets include a simple self-calculation of stroke risk (CHA_2_DS_2_-VASc score), personal barriers to uptake of warfarin and discussion of personal goals for lifestyle changes. In addition, a self-monitoring diary, including diet, alcohol intake (in units), warfarin regimen and INR results is also provided.

To overcome the language barrier of the general Thai public toward English, the TREAT intervention was culturally adapted to fit the local context and then translated. Forward and backward translation by two bilingual experts was performed. A test run of the Thai version of the TREAT intervention was conducted among patients with AF with a range of educational ability (Thai literacy level is 94%) and age levels. Patient feedback was incorporated to improve the usability of the Thai-version TREAT intervention.

A training session was conducted to prepare all study site coordinators (pharmacists and nurses) on how to deliver the intervention effectively. To avoid contamination, those who provide the TREAT intervention and those who provide usual care will be two different groups of pharmacists and nurses. The intervention will be delivered within 4 weeks of initiating warfarin. Intervention fidelity will be ensured by direct observation of random sessions at each centre by the trainer. Patients in the usual care group will receive training on the OAC management from the anticoagulation clinic, and patient information about AF and need for warfarin by a healthcare professional using the standard warfarin education checklist.

### Patient and public involvement

Patients or the public were not involved in the design, or conduct, or reporting, or dissemination plans of our research. The patients involved in the development of Thai version of the TREAT intervention.

### Outcome measures

The primary outcome is TTR at 12 months. Secondary outcomes include (1) TTR at 6 months; (2) thromboembolic and bleeding events from at 12 months; (3) composite MACE outcome of non-fatal MI, non-fatal stroke and cardiovascular death and all-cause mortality, in an exploratory analysis (combined and individually) at 12 months; (4) change in patients’ knowledge of AF from baseline to 6 months and 12 months; (5) cost effectiveness; (6) quality of life at baseline, 6 months and 12 months assessed using the 5-level EQ-5D version (EQ-5D-5L) (Thai version)^29 30^ and (7) patient satisfaction/perceptions of the TREAT intervention. An embedded qualitative study will assess patient perceptions of the TREAT intervention.

### Study procedures and schedules of assessment

Baseline SAMe-TT_2_R_2_ score will be calculated (table 1). All patients will receive warfarin, dose adjusted to achieve a target INR of 2.0–3.0. INR monitoring will be undertaken at routine intervals (as would occur in usual care) and will be recorded over a 12-month period. Patients will be randomised as described in figure 1, either to Group 1 (usual care) or Group 2 (intervention arm), for which the trial is powered. Group 2 is a SAMe-TT_2_R_2_ scores directed management group based on a: patients with AF likelihood of achieving and maintaining optimal TTR (SAMe-TT_2_R_2_ scores 0–2; Group 2a) and those likely to achieve poor TTR (SAMe-TT_2_R_2_ scores>2, Group 2b). From our prior data, approximately 15%–20% will likely enter Group 2a. The primary and secondary outcomes between Group 1 and Group 2 (together) will be compared. The schedule of assessment is presented in table 2. INR monitoring is independent of the intervention (ie, naturalistic) as we recognise that the improvement of TTR may be a result of more frequent monitoring. Patients in all groups will have their INR monitored as they would if they were not in the trial (by anticoagulation services which are separate from the trial and who are blinded to treatment allocation).

**Table 2 T2:** Study visits schedule

**Clinical assessment** Demographic information: age, sex, ethnicity, education level, height (cm), weight (kg), body mass index, smoking status and alcohol use Medical history: history of arterial hypertension, heart failure, diabetes mellitus, coronary artery disease (myocardial infarction, PCI and CABG), peripheral artery disease, stroke, transient ischaemic attack, systemic embolism, COPD, chronic kidney disease, chronic liver disease, thyroid disease and bleeding event Physical examination, blood pressure, heart rate, EHRA and NYHA class Concomitant medical therapy					
**OAC therapy education:** all patients—a standard OAC education session conducted by a healthcare professional about the clinical significance and management of OAC therapy **Questionnaires:** atrial fibrillation knowledge questionnaires, patient satisfaction (Likert scale) and EQ-5D-5L (Thai version) **Health economics assessment:** EQ-5D-5L (Thai version), AF, warfarin and clinical event-related healthcare resource use and intervention costs					
**Follow-up of clinical events:** TTR, composite of thromboembolism, major bleeding and all-cause death (in all patients)					
	**Baseline**	**M1±7D**	**M2±7D**	**M6±14D**	**M12±14D**
Clinical assessment	**a, b, c, d**	**c**	**c**	**c**	**c, d**
ECG	x				
INR**	x	x	x	x	x
Standard OAC therapy education	x				
TREAT intervention		x			
Questionnaires	x			x	x
Qualitative assessment	x†			x	
Health economic assessment	x			x	x
Follow-up of clinical events				x	x

*INR monitoring is mandatory during the 12-month follow-up period for all patients, with frequency as per usual care conducted by anticoagulation clinics.

†Baseline interviews of patients will take place within 4 weeks of receiving the intervention.

AF, atrial fibrillation; CABG, coronary artery bypass grafting; COPD, chronic obstructive pulmonary disease; ECG, electrocardiogram; EQ-5D-5L, The 5-level EQ-5D version; INR, international normalised ratio; OAC, oral anticoagulants; PCI, percutaneous coronary intervention.

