### Sample size and power calculations

Most recent studies suggest that the mean TTR in Thai patients receiving warfarin is in the range of 50%–55%.^11 12^ Since an improvement of 10% in the mean TTR is likely to be clinically meaningful, we assume a 10% difference in 12-month TTR with 90% power and 5% significance level for our sample size calculation and using an SD of ‘26’ as observed in a previous Thai study to determine the sample size estimates. Hence, to detect a 10% mean difference in TTR at 12 months, using two-sided test, sample size for randomisation in a 1:1 ratio would be 288 or 144 per arm. Assuming and adjusting for a 10% attrition/loss to follow-up rate, a total sample size of 320 patients or 160 per arm is needed.

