#### Subgroup analysis

Subgroup analyses will be conducted for the stratification variable sex only. All other stratification variables will be used only to ensure that the two groups are balanced in terms of these important variables. Subgroup analyses will be limited to the primary outcome only. Tests for statistical heterogeneity (eg, by including the treatment group by subgroup interaction parameter in the regression model) will be performed prior to any examination of effect estimates within subgroups. The results of subgroup analyses will be treated with caution and will be used for the purposes of hypothesis generation only.

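### The 90% power is right for the strategy contrast, but 15–20% of Group 2 get control care, and no analysis is planned in score >2 patients, the only ones whose care differs.

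*Protocol article*

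**What the plan says.** Randomisation: Group 1 is warfarin with usual care. Within Group 2, a score of 0–2 (Group 2a) also leads to warfarin with usual care, and only a score above 2 (Group 2b) leads to TREAT. Randomisation is stratified by score (0–2, 3–5, 6–8), centre and sex.

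Study procedures and schedules of assessment: "From our prior data, approximately 15%–20% will likely enter Group 2a", and "The primary and secondary outcomes between Group 1 and Group 2 (together) will be compared". The same section names Group 1 versus Group 2 as the contrast for which the trial is powered.

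Sample size and power calculations: "we assume a 10% difference in 12-month TTR with 90% power and 5% significance level", "using an SD of ‘26’ as observed in a previous Thai study", giving "sample size for randomisation in a 1:1 ratio would be 288 or 144 per arm". The section does not mention the share of Group 2 that does not receive TREAT.

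Subgroup analysis: subgroups are examined by sex only. Of the remaining stratification variables, which include the score, it says "All other stratification variables will be used only to ensure that the two groups are balanced in terms of these important variables".

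**The concern.** Score 0–2 patients receive the same care in both arms, so their expected difference in TTR is zero by design. They stay in the primary comparison, which therefore averages the effect of TREAT in recipients with a zero in everyone else.

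That average is the right quantity for a score-guided strategy. The Introduction, however, also argues for TREAT itself, as a help to patients predicted to have poor control, and no planned clinical analysis estimates its effect in those patients. The protocol does not merely leave this open: the Subgroup analysis section rules it out. A null or modest pooled result could then be read as a failure of TREAT, and a score >2 analysis added afterwards would be post hoc.

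The score also interferes with the one subgroup analysis that is kept. Non-Caucasian race scores 2 and female sex scores 1, so no Thai woman can score 0–2. Every Group 2 patient left without TREAT by design is a man.

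**Working it through.** **Inputs.** Difference 10 points, SD 26, two-sided 5%, 90% power, 144 evaluable per arm, 10% attrition (Sample size and power calculations). Share with score 0–2: p = 0.15 to 0.20 (Study procedures), taken as the share within each arm because randomisation is stratified by score. Earlier TREAT effect at 6 months: 78.5 − 66.7 = 11.8 points (Introduction).

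**The plan's own figure.**
- n per arm = 2 × (1.960 + 1.282)² × 26² / 10² ≈ 142.1, so 143. The t-test version gives 143.03, so 144 per arm and 288 in total.
- 288 / 0.90 = 320. The stated numbers reproduce.
- SE = 26 × √(2/144) = 3.064. Power = Φ(10/3.064 − 1.960) = 90.4%.

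**What 10 points across the arm implies in recipients.** Arm difference = (1 − p) × TREAT effect. So TREAT effect = 10/0.85 = 11.8 points, or 10/0.80 = 12.5 points.

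**Power by size of the TREAT effect.** Pooled power uses SE 3.064. The score >2 analysis has 144 × (1 − p) = 122.4 or 115.2 per arm, with SE = 26 × √(2/122.4) = 3.324 or 26 × √(2/115.2) = 3.426.

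| TREAT effect in recipients | p | Pooled difference | Pooled power | Score >2 power |
|---|---|---|---|---|
| 10 | 0.15 | 8.50 | 79.2% | 85.3% |
| 10 | 0.20 | 8.00 | 74.2% | 83.1% |
| 11.8 | 0.15 | 10.03 | 90.5% | 94.4% |
| 11.8 | 0.20 | 9.44 | 86.9% | 93.1% |

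The score >2 analysis has the higher power in every row despite using fewer patients.

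**Sex subgroup.** By Table 1 in the Introduction, a Thai woman scores at least 2 + 1 = 3. The protocol does not give the share of men, so assume 50–60%. The share of men with score 0–2 is then between 0.15/0.60 = 25% and 0.20/0.50 = 40%. A uniform 10-point TREAT effect would appear as 10 points in women and as 10 × 0.75 = 7.5 down to 10 × 0.60 = 6.0 points in men. That gap of 2.5 to 4.0 points would come from the allocation rule alone.

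**If the 15–20% is a share of all randomised patients.** The protocol does not state the denominator. On this reading 30–40% of Group 2 would not receive TREAT, a 10-point TREAT effect would give 7.0 or 6.0 points across the arm, and pooled power would be about 63% or 50%.

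**The case against.** The strongest reply is that this is a strategy trial. The objective is the score-guided strategy plus education against usual care, and leaving predicted good responders on usual care is part of that strategy. Pooling is then the correct intention-to-treat contrast, and it is the one the protocol says it is powered for. This stands. A reader might infer that the stated 90% is wrong; the documents do not support that, because the figure is claimed for Group 1 versus Group 2 and reproduces for it.

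The 74–79% is also only one scenario. The protocol calls 10 points a clinically meaningful difference in mean TTR; it does not predict 10 points in recipients. At 11.8 points, the only TREAT effect the document gives, there is little or no shortfall. That effect was measured at 6 months, however, and the primary outcome is at 12 months after a one-time intervention, so the design has little room for waning. The planned adjustment for stratification variables may bring the residual SD below 26, by an amount that cannot be derived from the document.

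Two further inferences fail. A score >2 analysis would not restore 90% power at 10 points: it reaches 83–85%, because it drops 15–20% of patients. Nor is the cost-effectiveness ratio diluted. With no TREAT cost and no TREAT effect in score 0–2 patients, incremental cost and incremental QALYs both shrink by (1 − p), so the expected ratio is unchanged and only precision suffers.

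Finally, limiting subgroups to sex is a defensible restraint in a plan without multiplicity adjustment. But score is a baseline variable and randomisation is stratified at this cut, so the score >2 contrast is a randomised comparison, and it is the one in which care actually differs.

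**Conclusion.** The sample size, the power for the strategy contrast and the primary analysis are sound. Two things are badly fixed. First, the protocol does not say that its 10 points is an average over an arm in which 15–20% get control care, which implies 11.8–12.5 points in recipients. Unadjusted pooled power to detect a TREAT effect is about 74–79% if that effect is 10 points and 86.9–90.5% if it is 11.8. Second, the sex-only rule excludes the score >2 estimate and leaves a sex comparison in which a uniform TREAT effect would look smaller in men.

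These figures assume SD 26, 144 evaluable per arm, 15–20% with score 0–2 in each arm and no effect in those patients. The size of the sex artefact also rests on the assumed share of men; its direction follows from the scoring table. This is a worthwhile and nearly free improvement. It does not invalidate the trial's main conclusion.

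**What to change.** 1. Keep Group 1 versus all of Group 2, by intention to treat, as the primary analysis.
2. Amend the Subgroup analysis section to prespecify, before the final analysis, one supporting analysis: 12-month TTR among randomised patients with score >2, analysed as allocated and adjusted for the stratification variables. Give its expected size (about 115–122 per arm) and power (83–85% at 10 points, 93–94% at 11.8).
3. State that the sex subgroup will be read alongside that analysis, because all score 0–2 patients are men.
4. Add to Sample size and power calculations that the 10 points is an arm-average difference implying 11.8–12.5 points in recipients. Give the denominator of the 15–20%.

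Cost: one extra regression without multiplicity control, to be labelled as supporting, and a less favourable power statement for TREAT itself. No further patients or data are needed. The Trial status section expected recruitment to end in May 2021, so changing the analysis wording is the practical route.
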